This fact and the results from the references in chapter 2 formed the idea to investigate a study to obtain preliminary information on the safety and efficacy of two induction treatment protocols – ATG-Fresenius S as a bolus regimen and Thymoglobulin in standard application – in immunological risk patients under basal immunosuppression with Tacrolimus, MMF and steroids used in the prevention of acute rejection following renal transplantation.

All AE will be documented but not all AE's will be classified as primary endpoint.

The trial will be performed as a pilot trial to compare tolerance, side effects and efficacy of ATG-Fresenius S compared to Thymoglobulin.

Clinical equivalence of ATG-Fresenius S to Thymoglobulin will be assumed up to a difference rejection in rates of  $\pm 15\%$  absolute.

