## **4. TRIAL DESIGN**

### **4.1 Type of study, description of study design**

The trial is planned as a multicenter, 1:1 randomised, parallel group, comparative, open study. The study may be expanded to other Swiss or a foreign state centers. The patients included into the study will receive standard immunosuppression therapy consisting of Tacrolimus / MMF / steroids / IVIG / ATG-Fresenius S bolus therapy in one arm and in the other arm Tacrolimus / MMF / steroids / IVIG / Thymoglobulin, respectively.

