## 6. TREATMENT OF SUBJECTS

### 6.1 Administration route, single dose, dosage, treatment period, follow-up for subjects

All patients included will provide written informed consent to participate in the trial.

Blood parameters will be determined before study drug administration which will be used as baseline values.

In women of childbearing age a pregnancy test will be performed before inclusion.

Patients qualified for the trial will be randomised to one or the other treatment.

The treatments will be administered as open therapies. A central venous catheter will be placed and kept open using a normal saline or glucose infusion drip or a fistula. This line will be used to administer test treatments.

Intravenous methylprednisolone sodium succinate (see table "therapy scheme I and II") should be given 1 hour before administering the test drugs.

Patients randomised to receive a bolus therapy with ATG-Fresenius S will be treated i.v. with a 9 mg/kg bw bolus of ATG-Fresenius S, which is diluted in 100-500 ml physiological saline. The infusion has to be applied completely before reperfusion (infusion time at least 1 hour). After this first infusion the patients receive 3 mg/kg bw/d for 4 days given over 4 hours.

Patients randomized to receive Thymoglobulin will be treated i.v. with 1.5 mg/kg bw of Thymoglobulin, which is diluted in 100-500 ml physiological saline. The infusion has to be completed before reperfusion (infusion time at least 1 hour). After this first infusion the patients receive 1.5 mg/kg bw/d for 3 days given over 4 hours.

The patients will be observed closely for the first 2 hours of treatment.

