**Optional monitoring:**

- Protocol allograft biopsies will be done on day 7 post-transplant, at month 3, 6, and 12.
- Lymphocyte subpopulations consisting of cells positive for CD3, CD4, CD8, CD19, and CD56 will be measured by flow-cytometry before transplantation, daily for the first 7 days, at month 1, 3, 6, 12, and 24.
- Monitoring for viral infection/reactivation (e.g. Decoy cells in urine, Polyoma-BK-viremia, EBV-viremia, CMV-antigenemia or CMV-viremia).

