**6.3. Diagnosis and treatment of rejection episodes**

Clinical acute rejection episodes are defined by an increase of serum creatinine of >20% from baseline with consisting histology classified according to local practice.

Subclinical acute rejection episodes are defined by a protocol biopsy with consisting histology classified according to local practice.

The treatment of rejections is ad libidum of the physician, however, a cross-over treatment as rescue-therapy by using the immunoglobulin preparation (AFG-Fresenius S or Thymoglobulin) from the other group is prohibited.

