**5 = assessment impossible**

- the available data are insufficient for any reasonable assessment with respect to a causal connection

In this open-label trial the causality assessments of all adverse events will be provided by blind raters. The rater will receive all information available for a particular adverse event, including predisposing factors from the patients' history, concomitant medication and diseases, but he/she will be unaware of the investigational treatment actually received. For each adverse event two different causality assessments will be obtained: (a) assuming that the patient has received ATG and (b) assuming that he/she has received Thymoglobulin. During data analysis only the assessment corresponding to the treatment actually received will be used.

All cases where 1, 2 or 3 applies will be evaluated as attributable adverse events / ADRs.

All adverse events, i. e. also the already known ADRs, must be documented and serious adverse events also be registered. There is also an obligation to registration if a causal relationship is not supposed resp. not evident. The following items must be registered:

- Precise trial subject data;
- precise description of the AE;
- precise recording of the time of the AE in relation to the course of therapy;
- intensity of the AE;
- results of diagnostic and therapeutic measures,
- where applicable, rechallenge and/or dechallenge data;
- course and outcome of the AE;
- severity of the AE, including medical assessment;
- all other important data that may be of relevance for assessment of a possible relationship between the AE and the administration of the investigational medical substance.

Data are documented and registered on the form "adverse events" or „serious adverse events“ (see enclosure 4), whereby the needed additional information can be supplied without a specific form.

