- Number of rejections per patient (Mann-Whitney U-Test).
- Duration of rejection episodes (t-test).
- 12, and 24-months graft survival rate (Chi-square statistic).
- 12 and 24-months patient survival rate (Chi-square statistic).
- Number of prednisone pulses within 12 and 24 months (Mann-Whitney U-Test).
- Rejection reversal rate (Chi-square statistic).

The analysis of efficacy will be based on the full analysis set (FAS) which includes all patients who were randomized and treated and for whom any post-treatment efficacy data are available.

After completion of the 24-months follow-up period the final biometrical analysis will be performed.

Furthermore, all patient data recorded in the trial database will be tabulated by treatment group using methods of descriptive data analysis, with specification of summary statistics applicable to their levels of measurement.

Sample size estimation:

In this pilot study the determination of the sample sized is based primarily on feasibility rather than on statistical reasons. A total of 40 (Zürich 20, Basel 20) randomised and treated patients (20 in each treatment group) will be included.

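### The protocol does not specify that rejection biopsies are read masked to arm in this open trial, and a net change in the status of three patients moves the rejection difference by 15 points.

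*Protocol*

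**What the plan says.** Section 4.1: "The trial is planned as a multicenter, 1:1 randomised, parallel group, comparative, open study". Section 6.1 repeats it for the drugs: "The treatments will be administered as open therapies".

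Section 6.3 gives two rejection definitions. A clinical episode needs a creatinine rise of more than 20% "from baseline with consisting histology classified according to local practice". For the other kind, "Subclinical acute rejection episodes are defined by a protocol biopsy with consisting histology classified according to local practice". Section 6.2 schedules the biopsies under the heading of optional monitoring: "Protocol allograft biopsies will be done on day 7 post-transplant, at month 3, 6, and 12".

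Section 3 attaches a margin to rejection: "Clinical equivalence of ATG-Fresenius S to Thymoglobulin will be assumed up to a difference rejection in rates of" ±15% absolute. Section 4.3.2 lists rejection incidence and type as secondary endpoints. Section 9 analyses incidence by chi-square, along with time to first and second rejection, number per patient, duration and reversal rate.

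Masking is specified for one judgement only. Section 7.3 g says: "In this open-label trial the causality assessments of all adverse events will be provided by blind raters". Section 4.2 adds that Basel and Zürich assess each other's adverse events without knowing the treatment. No section extends this to histology, and none provides for a central or second reader.

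**The concern.** Histology involves judgement, and borderline lesions leave most room for it. In an open trial, a reader who knows the induction product may be influenced by what is expected of it. The protocol itself states such expectations: section 2.5.2 describes ATG-Fresenius S as milder and more selective, and section 3 assumes that the two treatments are equally effective.

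Subclinical episodes are the most exposed, because no creatinine rise or other sign has to agree with the reading. Rejection is also the only outcome to which the protocol attaches an equivalence margin, and several analyses in section 9 depend on it.

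This cannot be left to an analysis plan. What the reader knows is settled when the slide is read, and no later analysis of the recorded category can restore masking. A confidence interval shows sampling error but gives no sign of a reading that leans towards one arm.

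**Working it through.** **Inputs**
- Patients per arm: n = 20. Section 9 states that 40 "randomised and treated patients (20 in each treatment group) will be included".
- Margin: 15 percentage points (section 3).
- Unit of analysis for incidence: the patient with at least one rejection episode. I assume that subclinical episodes count. Section 9 does not separate the two kinds, and if they are reported apart the same arithmetic applies to each.

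**The plan's own figure.** The sample size is 2 × 20 = 40, set on feasibility. No alpha, power or rejection rate is given, so there is nothing further to reproduce.

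**Effect of a changed status.** If k1 and k2 are the net numbers of patients added to the rejection count in each arm, the shift in the difference is (k1 − k2)/20.

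| k1 | k2 | Shift in difference |
|---|---|---|
| 1 | 0 | 1/20 = 5 points |
| 2 | 0 | 2/20 = 10 points |
| 3 | 0 | 3/20 = 15 points |
| 2 | −1 | 3/20 = 15 points |
| 2 | 1 | 1/20 = 5 points |

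The last row shows that changes in the same direction in both arms partly cancel. If fewer patients are evaluable in the affected arm, each weighs more. As assumed examples, 3/18 = 16.7 points and 3/16 = 18.8 points.

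**Set against sampling error.** Newcombe's interval for a difference d = p1 − p2, with Wilson limits l and u for each arm, runs from d − √[(p1 − l1)² + (u2 − p2)²] to d + √[(u1 − p1)² + (p2 − l2)²]. The event counts below are assumed for illustration.

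- Wilson limits: 6/20 gives 0.146 to 0.519; 9/20 gives 0.258 to 0.658.
- 6/20 against 6/20: d = 0, 95% CI −26.8 to +26.8 points.
- 9/20 against 6/20 (three patients changed in one arm): d = +15.0, 95% CI −14.1 to +40.9 points.
- Other equal splits with no reading error: ±16.1 points at 0/20 and ±28.4 points at 10/20. At every equal split tried, from 0/20 to 13/20, the interval is wider than ±15.

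So three changed patients move the point estimate by the full width of the margin, while the interval already exceeds the margin without any reading error.

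**The case against.** Several counter-arguments have force.

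- **Silence is not a rule.** Section 6.3 speaks of how histology is classified. It does not say who reads the slide or what that person is told. A reader might infer that the protocol prescribes an unmasked reading; it does not. What stands is that nothing in it prevents one.
- **The comparison with adverse events is not exact.** Only attribution to the drug is masked. The diagnosis is not: section 4.3.1 makes anaphylaxis and serum sickness clinical diagnoses. The masked step also serves the primary endpoint. This weakens any charge of inconsistency. It remains true that the protocol guards against open-label bias in one judgement and is silent on another.
- **Patients count, not slides.** A reader might infer that three biopsies read differently are enough. They are not, unless they belong to three different patients, each reading changes whether that patient has ever rejected, and the net effect runs one way. A patient already counted from another biopsy adds nothing. The protocol gives no misreading rate, so the likelihood of such a shift cannot be stated.
- **The consequence is limited.** Rejection is secondary, all analyses are descriptive, and section 9 sets no equivalence test against the margin. A reader might infer that reader bias would overturn an equivalence conclusion. The document plans no such test, and the intervals above would not fit within ±15 anyway. The margin serves here only as a yardstick of size.
- **The remedy is partial.** Clinicians who know the arm still decide on for-cause biopsies and on rejection treatment, and protocol biopsies are optional. Masking the reader changes none of this, so counts of steroid pulses stay exposed.

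Section 4.3.2 names the Banff classification while section 6.3 refers to local practice. The two should be reconciled, but that is a separate matter and neither masks the reader.

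**Conclusion.** The point holds as a gap worth closing at low cost. The trial is open, both rejection definitions rest on locally classified histology, subclinical rejection rests on nothing else, and masking of the reader is not specified.

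The size is 5 points per patient whose status changes, and 15 points for a net three patients in one direction. This assumes 20 evaluable patients per arm and an incidence that counts patients. It describes how sensitive the estimate is, and does not predict that such misreading will occur.

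What is at stake is bias in the preliminary efficacy estimate that section 3 sets out to obtain. The primary safety endpoint does not depend on it.

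**What to change.** Add to section 6.3:
- Biopsies go to the same local pathologist under the trial number, with a request that omits the arm, the induction product and the infusion days.
- The rejection category from that reading is entered on the CRF before any disclosure of treatment, and is the category used in section 9.
- If the pathologist has to be told the treatment for patient care, this is logged with its date.

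The cost is a coded request form at each centre, a short protocol addition and a log of occasional unmasking. No extra reader or biopsy is needed, and patient care is unchanged. Because the decisions to biopsy and to treat are still made with knowledge of the arm, the report should say so when it presents rejection and pulse counts.

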**6.4. Prophylaxis and treatment of infections****A) Pneumocystis carinii**

As prophylaxis it is recommended to administer Cotrimoxazole double strength 1 Tbl. 3x/week for 6 months. Alternatively an inhalation of Pentamidin once a month for 6 months can be given.

**B) CMV**

CMV constellation R-/D- will not receive prophylaxis. In all other constellations (R+/D-, R+/D+, R-/D+) prophylaxis with valgancyclovir p.o. (900mg/day adapted to renal function) will be done for 3 months.

CMV disease is defined according to Ljungman CID 2002 and Preiksaitis AJT 2004, respectively.

**THERAPY SCHEME I**

(ATG-Fresenius S GROUP)

| Period                           | ATG-Fresenius S                                                            | IVIG                                                                                                 | Tacrolimus                                                 | MMF                                                         | Prednison                                                                                       |
|----------------------------------|----------------------------------------------------------------------------|------------------------------------------------------------------------------------------------------|------------------------------------------------------------|-------------------------------------------------------------|-------------------------------------------------------------------------------------------------|
| Day -1
(if applicable) | -                                                                          |                                                                                                      | 0.2 mg/kg/d                                                | 1000 mg p.o.                                                | -                                                                                               |
| Day 0
(operation)      | 9 mg/kg bw infusion
The infusion has to be completed before reperfusion | 0.4 g/kg bw given pre-operatively or post-operatively as soon as possible (maximal total dose 140 g) | 0.2 mg/kg/d                                                | 2 x 1000 mg/d p.o.                                          | 1000 mg Methylprednisolone i.v.
Has to be completely infused before ATG-Fresenius S is given |
| Day 1                     | 3 mg/kg bw i.v. *                                                          | 0.4 g/kg bw                                                                                          | 0.2 mg/kg/d                                                | 2 x 1000 mg/d p.o                                           | 500 mg MP i.v.                                                                                  |
| Day 2                     | 3 mg/kg bw i.v. *                                                          | 0.4 g/kg bw                                                                                          | 0.2 mg/kg/d                                                | 2 x 1000 mg/d p.o                                           | 250 mg MP i.v.                                                                                  |
| Day 3                     | 3 mg/kg bw i.v. *                                                          | 0.4 g/kg bw                                                                                          | 0.2 mg/kg/d                                                | 2 x 1000 mg/d p.o                                           | 0.5 mg/kg/d p.o.
rounded to 5 mg (downwards)                                                 |
| Day 4                     | 3 mg/kg bw i.v. *                                                          | 0.4 g/kg bw                                                                                          | 0.2 mg/kg/d                                                | Dose adjustment to target blood levels and white cell count | Dose adaption (see below)                                                                       |
| Day 5                     | -                                                                          |                                                                                                      | 0.2 mg/kg/d then adjust to target blood levels (see below) | Dose adjustment to target blood levels and white cell count | Dose adaption (see below)                                                                       |
| Day 6                     | -                                                                          |                                                                                                      | Adjusted to target blood levels (see below)                | Dose adjustment to target blood levels and white cell count | Dose adaption (see below)                                                                       |

\* (dose adaptation see below)

**THERAPY SCHEME II**  
 (Thymoglobulin GROUP)

| Period                           | Thymoglobulin                                                                | IVIG                                                                                              | Tacrolimus                                                 | MMF                                                         | Prednison                                                                                     |
|----------------------------------|------------------------------------------------------------------------------|---------------------------------------------------------------------------------------------------|------------------------------------------------------------|-------------------------------------------------------------|-----------------------------------------------------------------------------------------------|
| Day -1
(if applicable) | -                                                                            |                                                                                                   | 0.2 mg/kg/d                                                | 1000 mg p.o.                                                | -                                                                                             |
| Day 0
(operation)      | 1.5 mg/kg bw infusion
The infusion has to be completed before reperfusion | 0.4 g/kg bw given preoperatively or postoperatively as soon as possible (maximal total dose 140g) | 0.2 mg/kg/d                                                | 2 x 1000 mg/d p.o.                                          | 1000 mg Methylprednisolone i.v.
Has to be completely infused before Thymoglobulin is given |
| Day 1                     | 1.5 mg/kg infusion (dose adaptation see below)                               | 0.4 g/kg bw                                                                                       | 0.2 mg/kg/d                                                | 2x 1000mg/d p.o.                                            | 500 mg MP i.v.                                                                                |
| Day 2                     | 1.5 mg/kg infusion (dose adaptation see below)                               | 0.4 g/kg bw                                                                                       | 0.2 mg/kg/d                                                | 2x 1000mg/d p.o.                                            | 250 mg MP i.v.                                                                                |
| Day 3                     | 1.5 mg/kg infusion (dose adaptation see below)                               | 0.4 g/kg bw                                                                                       | 0.2 mg/kg/d                                                | 2x 1000mg/d p.o.                                            | 0.5 mg/kg/d p.o. rounded to 5 mg (downwards)                                                  |
| Day 4                     | -                                                                            | 0.4 g/kg bw                                                                                       | 0.2 mg/kg/d                                                | Dose adjustment to target blood levels and white cell count | Dose adaption (see below)                                                                     |
| Day 5                     | -                                                                            |                                                                                                   | 0.2 mg/kg/d then adjust to target blood levels (see below) | Dose adjustment to target blood levels and white cell count | Dose adaption (see below)                                                                     |
| Day 6                     | -                                                                            |                                                                                                   | Adjusted to target blood levels (see below)                | Dose adjustment to target blood levels and white cell count | Dose adaption (see below)                                                                     |

